### Time to resolution of the improvable clinical situation

Time to resolution will be estimated by the Kaplan–Meier method and comparisons will be done using the log-rank test. Multilevel survival analysis will be used to homogenize the data structure (Yau 2001). The analytical strategy is the same as described above: an initial model will be adjusted to estimate the intervention effect, introduce the professional-level variables (EQA, EQR, EQPF), and then determine whether the variables at the reminder level change the estimated intervention effect.

The level of significance will be established at 5 %. All analysis will be done using the Stata/SE software, version 11.2 (StataCorp 2012).

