### Objectives

#### Primary objectives

To determine the effectiveness of reminders compared to no reminders in improving adherence to multiple clinical recommendations measured as the resolution of the clinical condition that motivated the reminder, in a primary care setting with a well-established feedback system.

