#### Randomization

The PCC will be the unit of analysis, so that all professionals from the same centre will be assigned to the same arm of the trial. Randomization will be done with the Stata/SE (v. 11.2, StataCorp) module for the design of randomized clinical trials (Ryan 1990). With the goal of achieving a balanced distribution of the quality of care by PCC in each arm, centres will be stratified by the quintiles of EQA results in the month prior to study initiation. The procedure will consist of obtaining the ICS list of PCCs, importing the data in STAT format, applying the inclusion and exclusion criteria, and adding the EQA value for each PCC. The PCCs will be allocated in randomized blocks of 6, 12, and 18 to achieve the same number of PCCs in each of the study groups (Fig. 3).

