### Outcomes

The main outcome variable is the health professional’s adherence to the reminder, measured as the proportion of patients receiving the recommended attention (yes/no) and the time elapsed between the first reminder message and implementation of the recommended action (months). Reminders will be considered “resolved” when the professional has completed the recommended actions (Table 2).

**Table 2 Tab2:** Reminders seen by the health professional, corresponding clinical condition, and the resolution

Reminder	Clinical condition	Resolution
Control blood pressure	Arterial hypertension/Elevated cardiovascular risk	Most recent blood pressure reading within 1 year shows ≤140/90 mmHg or 150/95 mmHg, depending on cardiovascular risk status
Control glycated hemoglobin	Type 2 diabetes mellitus	Most recent glycaemia test within 1 year shows HbA1c ≤ 8 %
Control cholesterol	Cerebrovascular accident/ischemic heart disease	Most recent cholesterol test within 1 year shows LDL ≤120 mg/dl
Screen for retinopathy	Type 2 diabetes mellitus	Record of thorough eye examination within past 2 years
Encourage smoking cessation	Smoking habit	Last record says “non-smoker”
Vaccinate for hepatitis B	Hepatitis C	Record of vaccination
Treat with ACEI	Heart failure	Active ACEI/ARB prescription
Treat with beta blockers	Heart failure/Ischemic heart disease	Active beta blockers prescription
Treat with antiplatelet or anticoagulant drugs	Atrial fibrillation	Active prescription for antiplatelet or anticoagulant drugs, as appropriate
Treat with antiplatelet drugs	Cerebrovascular accident/Ischemic heart disease	Active antiplatelet prescription

*Hb* haemoglobin, *LDL* low-density lipoprotein, *ACEI* angiotensin-converting enzyme inhibitor, *ARB* angiotensin receptor blocker, *HbA1c* glycated haemoglobin

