### Resolution of the reminder

To estimate the effect of the intervention on improving the resolution of each reminder, a two-level analytical strategy will be used:Professional/PCC levelThe effect of the quality variables—EQA, EQR, and EQPF—on the resolution of the reminder will be evaluated at the aggregate level: percentage of reminders resolved. The Pearson correlation coefficient and scatter plots will be used for this purpose.Reminder levelHierarchical or multilevel methods will be used to take into account the structure of the information and be able to introduce variables from different levels as adjustment variables in estimating the intervention effect. Multilevel logistic regression models will be fitted. The analytical strategy will be to estimate the intervention effect, taking into consideration the randomized professionals; next, the effect size will be estimated by introducing the quality variables from the professional level (EQPF, EQA, and EQR). Finally, we will determine whether introducing variables from the reminder level changes the intervention effect. A subgroup analysis will also be done, by type of reminder.

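### The log-rank test named for comparing time to resolution ignores the cluster randomisation, and the plan does not say whether it or the multilevel survival model decides

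*Protocol article*

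**What the plan says.** The section on time to resolution states: "Time to resolution will be estimated by the Kaplan–Meier method and comparisons will be done using the log-rank test". No cluster adjustment of that test is mentioned. The next sentence adds: "Multilevel survival analysis will be used to homogenize the data structure". The paragraph then says that "an initial model will be adjusted to estimate the intervention effect", followed by models that add professional-level and then reminder-level variables, on the same strategy as for resolution. The significance level is 5%, and the text does not tie it to either method.

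The abstract commits to hierarchical modelling in general terms and places the logistic models for adherence at the level of the centre. For time it names only Kaplan–Meier and the log-rank test, again with the words "comparisons will be done using the log-rank test".

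Under Randomization, "all professionals from the same centre will be assigned to the same arm of the trial". The opening of Statistical analysis recognises correlation within patient, professional and centre. The section on resolution, whose strategy the time analysis borrows, describes the intervention effect as estimated "taking into consideration the randomized professionals".

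Outcomes puts both the yes/no resolution and the time to it in the main outcome variable, and the research hypothesis covers both. The primary objective names adherence only, "measured as the resolution of the clinical condition that motivated the reminder".

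**The concern.** The standard log-rank variance counts each reminder as a separate independent unit. In this trial arms differ by centre, and reminders from one centre share its patients, staff and habits. Chance differences between centres therefore appear as differences between arms, and the test takes them for signal. The distortion grows with the number of reminders per centre, which here runs to thousands for the pooled data. The Sample size section also declines to cap the number analysed.

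The plan gives the word for comparison to this test and the estimation of the effect to a multilevel model, without ranking them. An analyst could report the log-rank p-value as the time result and still be following the protocol. With two named methods, one of them invalid for the design, the choice could be made after the results are seen.

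**Working it through.** **The plan's own figures.** The protocol gives no error rate for the log-rank test, so there is none to reproduce. Its sample size does show that it expects clustering to matter. A comparison of 59% with 49% at alpha 0.01 and 95% power needs 882 reminders per group before inflation, and 882/0.9 = 980 after 10% loss. The stated 15,950 is 15,950/980 = 16.3 times that.

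**Inputs.**
- Reminders: the ten rows of Table 1 sum to 1,620,643 (estimated). The smallest type is ACEI/ARA2 treatment in heart failure, 11,394. Blood pressure has 534,702 and smoking 711,392.
- Clusters: 282 primary care teams (abstract). Leaving out the two pilot teams gives 280 and changes little.
- ICC at PCC level: 0.05 (Sample size), stated for the proportion resolved and not for time.
- Level: 5%; two-sided is assumed because the text does not say.

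**Formulas.** With m reminders per PCC, the design effect is DE = 1 + (m − 1) × ICC. Under the null hypothesis the unadjusted test statistic has standard deviation of about √DE instead of 1. The true size of a nominal 5% test is therefore 2 × [1 − Φ(1.96/√DE)].

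**Pooled reminders at ICC 0.05.** m = 1,620,643/282 = 5,747. DE = 1 + 5,746 × 0.05 = 288.3. √288.3 = 16.98 and 1.96/16.98 = 0.115, so the size is 0.908. The effective number of reminders is 1,620,643/288.3, about 5,600.

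| Data | m per PCC | ICC | DE | True size |
|---|---|---|---|---|
| All pooled | 5,747 | 0.05 | 288.3 | 0.91 |
| All pooled | 5,747 | 0.01 | 58.5 | 0.80 |
| All pooled | 5,747 | 0.001 | 6.7 | 0.45 |
| Smoking only | 2,523 | 0.05 | 127.1 | 0.86 |
| Blood pressure only | 1,896 | 0.05 | 95.8 | 0.84 |
| Smallest type | 40.4 | 0.05 | 3.0 | 0.26 |
| Smallest type | 40.4 | 0.01 | 1.4 | 0.10 |

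**Check by simulation.** 2,000 null trials were simulated with four arms of 70 PCCs of equal size, a monthly log-rank test over 12 months, and PCC resolution rates varying around 49%. At ICC 0.05 with pooled reminders, one pair of arms was rejected in 0.91 of trials, in agreement with the formula. The four-arm test was rejected in 0.999. At least one of the three comparisons with control was rejected in more than 0.99. For the smallest reminder type one pair was rejected in 0.26.

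**The case against.** The strongest reply is that the plan already handles clustering. The sentences after the log-rank test plan a multilevel survival model that estimates the intervention effect. The opening of Statistical analysis and the abstract both commit to hierarchical modelling that includes the centre. This stands, and it limits the finding. A reader might infer that the plan as a whole treats 1.6 million reminders as independent, so that a false positive on time is almost assured. The documents do not support that: the inflation follows only if the log-rank p-value is the one used.

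A reader might also infer from the phrase about randomised professionals that the models stop at a professional-level effect and leave out the centre. The protocol describes no such model. The abstract places the logistic models at centre level, Randomization calls the PCC the unit of analysis, and Statistical analysis names correlation within the centre. The phrase is imprecise wording, and no error rate should be attached to it.

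The 91% is also the pooled case. The plan emphasises each type of reminder, and eight of the ten types have far fewer reminders per PCC than blood pressure or smoking. The ICC for time is not given. Both points stand as to size, but even the smallest type has about five times the nominal error at the stated ICC.

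The primary objective and the sample size rest on resolution alone, which lowers the weight of time without removing it from the main outcome variable.

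Finally, a condensed article may leave model details to a fuller document. That would excuse silence. It does not excuse naming an unsuitable test as the comparison, in the methods and again in the abstract.

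**Conclusion.** The point holds in a limited form. The protocol states a comparison for time that does not fit its cluster design, sets a suitable model beside it, and does not say which one decides. The abstract names only the unsuitable one specifically for time. If the log-rank p-value were used, one nominal 5% comparison would have a true type I error between about 45% and 91% for pooled reminders across ICCs of 0.001 to 0.05, and about 26% for the smallest type at 0.05.

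These sizes assume a two-sided test, equal cluster sizes, clustering at PCC level only, the Table 1 estimates, and an ICC for time like the one stated for the proportion. Unequal cluster sizes would raise the inflation; stratification by EQA quintile could lower it somewhat. A multilevel survival model with a PCC term is meant to remove the inflation; its own error rate was not simulated.

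**What to change.** 1. Keep the Kaplan–Meier curves as description.
2. Drop the unadjusted log-rank test, or replace it with a cluster-adjusted version or a permutation test at PCC level.
3. State that the arm comparison for time comes from the planned multilevel survival model with a PCC-level random effect.
4. Align the abstract with this.
5. In the section on resolution, replace the reference to randomised professionals with randomised PCCs, so that the PCC level is explicit in the models for both resolution and time.

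This takes a few sentences of analysis wording. It needs no new data and no change of design. The price is wider confidence intervals for time than an unadjusted analysis would show, but valid ones.

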### Research ethics

The study design followed ethical guidelines contained in national legislation and the international standards defined in the Declaration of Helsinki and Tokyo. The study protocol was approved by the Committee on Clinical Research Ethics of the Jordi Gol Institute on Research in Primary Care (*Institut Universitàri d’Investigació en Atenció Primària*, IDIAP Jordi Gol).

All data extracted from the electronic health records system to create the reminders, as well as all data collected during the study for later analysis, will be anonymized so that it will be impossible for the research team to identify individual patients of the participating health professionals. A computer algorithm will be used that shows patient identification only to the primary care professionals (physicians and nurses) responsible for the patient’s care.

Patients are only indirectly affected by the trial because the researchers are not involved in any intervention or interaction with patients, all patient data are anonymized in accordance with national data privacy laws and National Health System policy, and the intervention is based entirely on best practice recommendations drawn from existing scientific evidence, published in clinical practice guidelines, and included in the objectives of the Catalan government’s Health Plan (*Pla de Salut*). Indeed, if the intervention results in better adherence by health professionals in the ICS primary care network to these evidenced-based recommendations, patients will benefit from the outcomes achieved by this clinical trial.

### Study oversight

There isn’t an independent data monitoring or trial steering committee.

## Discussion

The results of the present clinical trial will contribute new evidence on the impact of computerized point-of-care reminders on the adherence to clinical recommendations by primary care professionals, using an established feedback system. The study will involve almost all health professionals in the ICS primary care network and the population they serve, and therefore will be highly representative of clinical practice in the primary care setting. If the intervention is shown to be effective, the improvements should be almost immediately apparent, benefiting almost 5 million patients in the National Health System in Catalonia. Since the interventions will involve a high number of patients, small improvements in effectiveness could have a great impact on population health, according to the literature, both in terms of direct benefit and side effects. For example, increased use of antiplatelet therapy in patients with cerebrovascular disease reduces the number of coronary or cerebrovascular episodes and the associated mortality, but the number of haemorrhages also increases as a consequence of the treatment. To avoid undesirable effects to the extent possible, we selected indicators for which risk–benefit analysis has provided evidence that clearly favours the intervention.

Previously published studies have described better effectiveness when the feedback is a response to low adherence to clinical practice guidelines (Jamtvedt et al. 2003). In our study population, there is no low level of adherence to recommendations concerning the conditions we are studying, because health professionals have already been receiving performance feedback and lists of patients for 5 years during which their indicators have raised significantly. On the other hand, in contrast to many of the published studies, our design adds the reminders to an established feedback system that will be used in all arms of the study; this may lead to a smaller effect size. Holt et al. compared the use of reminders to a control group with no supporting tools (Holt et al. 2012). Therefore, we selected a 10 % intervention effect as clinically relevant.

Our study has some limitations. Some authors have suggested that “pay for performance” incentives may lead to better recording rather than better clinical practice (Bell and Levinson 2007; Petersen et al. 2006). A Cochrane review concluded that despite the increasing growth in this type of payment system, there is insufficient evidence for or against any impact on improving primary health care services (Scott et al. 2011). The compensation for objectives related to the indicators included in the intervention is low, not exceeding 750 euros per physician and 380 euros per nurse. In any case, this effect would occur in both the control group and the intervention groups; therefore, it would be unlikely to have an impact on the results that may be obtained. On the other hand, most of the selected indicators would not be susceptible to manipulation because they are based on laboratory results such as LDL cholesterol levels or HbA1c levels in patients with diabetes, or prescription data for specific drugs (e.g., antiplatelets, anticoagulants, beta-blockers, angiotensin-converting enzyme inhibitors). Therefore, it is likely that any recording changes would have real impact on health status.

Studies based on data from electronic health records can also be limited by the quality of the record, and any clinical records software such as ECAP could have a certain level of under-recording. Nonetheless, this limitation should affect both the intervention and control groups, and most of the reminders are related to health problems that are long-term indicators with a prevalence similar to what has been reported in the literature. This leads us to conclude that potential under-recording is not a major problem of the study design.

Finally, the health professionals participating in our study cannot be blinded to the intervention, which could possibly generate an information bias. Nonetheless, we selected cluster randomization because most studies of this type use this design; we decided against any design in which the same health professional would have some patient records with reminders and others without. In a study by Chambers et al. participants in one study arm received sporadic reminders about flu vaccine, others received them consistently, and a third group received no reminders (Chambers et al. 1991). The outcomes were worse for the sporadic reminders than for the control group, suggesting the hypothesis that health professionals become dependent on the reminder: if it does not appear, they may assume that the patient does not need the vaccine, which could result in a harm rather than a benefit to the patient.

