### Intervention

A maximum of 10 clinical reminders per patient will be offered, recommending actions related to at least one of the following nine clinical conditions: arterial hypertension, elevated cardiovascular risk, type 2 diabetes mellitus, cerebrovascular accident, ischemic heart disease, heart failure, atrial fibrillation, smoking habit, and hepatitis C. The reminders are integrated into the electronic health record for each patient so that they are available to any health professional who cares for the patient; the information is updated weekly to reflect any changes that occur.

Each reminder consists of the following information: an orange or red icon that codes the importance of the recommendation as moderate or high, respectively; the relevant clinical condition; the recommended action; and the date and value entered for the recommendation or related laboratory results. A recommendation is classified as highly important if treatment is required (red icon: e.g., atrial fibrillation, anticoagulant/antiplatelet treatment, 12/06/2011) and as moderately important if it refers to a variable, laboratory result, or vaccination (orange icon: e.g., Type 2 diabetes mellitus, monitor HbA1c, most recent value, 8.3, 12/05/2011) (Table 1).

**Table 1 Tab1:** Recommendations, clinical conditions, importance and estimated number of reminders

Recommendation (http://www.gencat.cat/ics/professionals/guies/mpoc/mpoc.htm)	Clinical condition	Importance	n (estimated)
Control blood pressure: ≤140/90 or ≥150/95, depending on risk status	Arterial hypertension/elevated cardiovascular risk	Moderate	534,702
Control glycaemia: HbA1c ≤ 8 %	Type 2 diabetes mellitus	Moderate	92,520
Control cholesterol: LDL < 120	Cerebrovascular accident/Ischemic heart disease	Moderate	90,060
Screen for retinopathy	Type 2 diabetes mellitus	Moderate	67,710
Smoking cessation within past year	Smoking habit	Moderate	711,392
Vaccination for hepatitis B	Hepatitis C	Moderate	14,534
ACEI/ARA2 treatment	Heart failure	High	11,394
Beta blockers treatment	Heart failure/Ischemic heart disease	High	69,155
Antiplatelet/anticoagulant treatment	Atrial fibrillation	High	16,260
Antiplatelet treatment	Cerebrovascular accident/Ischemic heart disease	High	12,916

*Hb* haemoglobin, *LDL* low-density lipoprotein, *ACEI* angiotensin-converting enzyme inhibitor, *ARB* angiotensin II receptor blocker

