Health professionals can also choose to view the reminders in their daily schedule of patients. The reminder provides a link to the patient’s electronic health record, from which the pertinent action can be taken (generate a prescription, record a vaccination, request a laboratory test, or record a clinical variable). There is also an option to ignore or exclude a recommendation for a particular patient and enter a comment about the reason for the exclusion.

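### About 77% of expected reminders resolve on a charted blood pressure or smoking entry and 18% on laboratory or prescription data, and the Discussion's reassurance does not reach recording induced by the reminder itself

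*Protocol article*

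**What the plan says.** The limitations part of the Discussion deals with recording in three steps.

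- On pay for performance, it says that "this effect would occur in both the control group and the intervention groups", so results are unlikely to be affected.
- On manipulation, it says that "most of the selected indicators would not be susceptible to manipulation because they are based on laboratory results", and adds prescription data to the same argument. It infers that changes in recording would probably reflect real changes in health.
- On under-recording in the electronic record, it says that "this limitation should affect both the intervention and control groups".

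Table 2 (Outcomes) fixes when a reminder counts as resolved. For blood pressure the rule is "Most recent blood pressure reading within 1 year shows ≤140/90 mmHg or 150/95 mmHg", depending on risk status. For smoking it is "Last record says “non-smoker". Two types resolve on a laboratory value (HbA1c, LDL) and four on an active prescription. The other two, retinopathy screening and hepatitis B vaccination, resolve on a record that the procedure was done.

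The Intervention section describes the reminder as a link to the patient's record, "from which the pertinent action can be taken (generate a prescription, record a vaccination, request a laboratory test, or record a clinical variable". The Control group section says that the usual feedback screen gives no direct interaction with the record and has to be sought out. Under Training, only intervention teams are trained for the trial.

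**The concern.** The Discussion's argument counts indicator types, but the plan's quantities count reminders. Sample size is stated as a number of reminders and a proportion resolved, and the main model is fitted at reminder level. The 6-month halting rule compares the main outcome between control and each intervention arm. If a few high-volume types dominate, the number of types says little about how exposed the overall result is to recording.

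The both-arms argument covers influences that the arms share. It says nothing about recording that the intervention itself provokes. A professional prompted during the visit may update the status of a patient who had already stopped smoking, or chart a reading for a controlled patient with none that year. Either turns an unresolved reminder into a resolved one without any change in smoking or blood pressure control.

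At stake is the interpretation of a positive result. The primary objective is resolution of the clinical condition, and a pooled difference could be partly a difference in charting. Conversely, a real gain in prescribing or laboratory control would be heavily diluted in the pooled figure.

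**Working it through.** The article gives no total or percentage on this point, so there is no stated figure to reproduce; its only quantity is the word for a majority. The check groups the Table 1 estimated counts by the Table 2 resolution rule.

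| Resolves on | Types | Reminders | Share |
|---|---|---|---|
| Charted blood pressure or smoking status | 2 | 534,702 + 711,392 = 1,246,094 | 76.9% |
| Laboratory value (HbA1c, LDL) | 2 | 92,520 + 90,060 = 182,580 | 11.3% |
| Active prescription | 4 | 11,394 + 69,155 + 16,260 + 12,916 = 109,725 | 6.8% |
| Record of eye examination or vaccination | 2 | 67,710 + 14,534 = 82,244 | 5.1% |
| All | 10 | 1,620,643 | 100% |

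Laboratory and prescription together: 182,580 + 109,725 = 292,305, and 292,305 / 1,620,643 = 18.0%. By type they are 6 of 10.

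**Effect on a pooled proportion.** With volume weights, a shift of *s* points in a group with share *w*, and nothing elsewhere, moves the pooled proportion by *s* × *w*. The shifts are assumed; the article gives no recording effect.

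- 5 points in blood pressure and smoking: 5 × 0.769 = 3.8 points pooled.
- Shift in both needed for the 10-point difference that the Sample size section calls clinically relevant: 10 / 0.769 = 13.0 points.
- Shift needed if only smoking moves (711,392 / 1,620,643 = 43.9%): 10 / 0.439 = 22.8 points.
- A true 10-point gain in every laboratory and prescription type only: 10 × 0.180 = 1.8 points.

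**Can a restricted analysis carry the question?** Assume all 282 teams are included, in four equal arms, with the article's ICC of 0.05 also holding in the subset. The design effect is 1 + (m − 1) × 0.05, where m is reminders per team.

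- All reminders: m = 1,620,643 / 282 = 5,747; design effect 288.3; per arm 405,161 / 288.3 = about 1,405 effective.
- Six types: m = 292,305 / 282 = about 1,037; design effect 52.8; per arm 73,076 / 52.8 = about 1,385 effective.

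For 59% against 49% at two-sided alpha 0.01, power is about 99.7% in both cases. At these cluster sizes the number of teams, not the number of reminders, limits precision.

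**What differs by arm.** Monthly scores, the incentive and patient lists (for 20 of the 25 recommendations) are common to all arms. Specific to the reminder arms are the prompt at the visit, its link to the record, and the training.

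**The case against.** The strongest reply is that the Discussion is not wrong as written. It speaks of indicators, and 6 of 10 do rest on laboratory or prescription data. The sentences on both arms concern the incentive and background under-recording, which are shared. Controls also have scores, money and patient lists, so they too have reason to update the chart. All of this stands. A reader might infer that the majority claim is false on the plan's own counts, that only the reminder arms are prompted, or that the both-arms sentences should be struck out. The documents support none of these. What the Discussion lacks is the weighting by volume and any treatment of recording that the intervention induces.

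A second reply is that analyses by reminder type are already planned (Abstract; Resolution of the reminder), so laboratory and prescription effects will be seen. This also stands, and it limits the harm to an all-reminder summary. The text is mixed on whether such a summary is the primary result: the Abstract points to type-by-type analysis, while the primary objective and the Sample size section point to a pooled one. Under the pooled reading, the by-type analysis is an addition, and no combined laboratory and prescription estimate stands beside the headline.

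A third reply is that recording alone does not resolve a blood pressure reminder, because the latest reading must be at target and measuring again is itself care. That is fair, and smoking status is the clearer case. The Discussion also concedes that lack of blinding may cause information bias, but it answers only by justifying cluster randomization.

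**Conclusion.** The concern holds in a limited form. The 76.9% and 18.0% shares follow exactly from Table 1. The Discussion's reassurance is true by type but covers under a fifth of expected reminders, so any all-reminder proportion, including those behind the sample size and the 6-month halting rule, is dominated by chart-entry outcomes. Recording induced by the prompt, the link and the training differs by arm, and the both-arms argument does not address it.

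A reader might go further and conclude that the result is biased in favour of reminders. That direction is plausible but not shown, since no passage gives a recording effect. The 13-point and 1.8-point figures show how large an assumed shift would have to be, or how far a gain would be diluted; they are not evidence that either will occur.

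The conclusion rests on three assumptions: that a pooled estimate is reported, that volume weights approximate what a multilevel logistic model gives, and that professionals enter blood pressure and smoking status. The last is a fair inference from Table 2 and the description of the link, but it is not stated outright.

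**What to change.** 1. Beside the all-reminder estimate, pre-specify as a sensitivity analysis the same multilevel logistic model restricted to the six laboratory or prescription types: HbA1c, LDL, ACEI/ARB, beta blockers, and the two antiplatelet or anticoagulant reminders.
2. Report by arm how often blood pressure and smoking status were recorded during follow-up, so that readers can see whether charting itself differed.
3. Qualify the Discussion. Limit the both-arms argument to the shared incentive and background under-recording, and limit the inference that recording changes reflect real health changes to laboratory and prescription outcomes. Say that the majority claim refers to types, and give the shares by volume.

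The cost is one extra model and one descriptive table on data already extracted, plus wording. Under the assumptions above, the restricted analysis loses almost no power. The downside is a more cautious headline if the two estimates differ. The restricted estimate need not be made a condition for declaring success; it is enough that it is fixed in advance and reported.
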